### Study design

This study is a single-center, assessor-blinded, data analyst-blinded, four-arm randomized controlled trial to be conducted at Shuguang Hospital Affiliated to Shanghai University of Traditional Chinese Medicine (TCM) in accordance with the Consolidated Standards of Reporting Trials (CONSORT) 2010 statement and the Standards for Reporting Interventions in Clinical Trials of Acupuncture (STRICTA) criteria (38, 39). A total of 132 participants will be recruited between October 2023 and October 2024, and randomly allocated to PQ exercise group (PQG), acupuncture group (AG), PQ exercise and acupuncture combined group (PAG), or control group (CG) at a 1:1:1:1 ratio. All participants will receive usual medical care and health education; those in the three intervention groups will receive PQ exercise, acupuncture treatment, or a combination of both treatments three times per week for 8 weeks. The primary outcome will be exercise endurance as assessed by a 6-min walk test (6MWT). Secondary outcomes will include lung function, degree of dyspnea, diaphragmatic function, respiratory muscle strength, skeletal muscle structure, skeletal muscle function, psychological states, and QoL. Exploratory outcomes will include the levels of inflammatory mediators. Outcomes will be measured within 1 week before and after the interventions. In addition, the frequency and severity of acute exacerbation of COPD (AECOPD) will be recorded at baseline and 1 year after intervention. A flow diagram of the study design is shown in Figure 1, and the study schedule is depicted in Table 1. This study has received ethics approval from Shuguang Hospital Affiliated to Shanghai University of TCM (approval number 2023–1360–127-01), and it has been registered in the Chinese Clinical Trial Registry (ChiCTR2300076255). The study protocol strictly follows the Standard Protocol Items: Recommendations for Interventional Trials (SPIRIT) checklist (Supplementary File 1).

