**Figure 1 fig1:**
[figure not shown]
Flow diagram of the study. The template is from the CONSORT 2010 flow diagram. CG, control group; PQG, pulmonary-based Qigong group; AG, acupuncture group; PAG, pulmonary-based Qigong exercise and acupuncture combined group; HC, health education and conventional medical treatment; AT, acupuncture treatment; 6MWD, 6-min walking distance; IL, interleukin; NLRP3, NOD-like receptor protein 3; ASC, apoptosis-associated speck-like protein containing a C-terminal caspase recruitment domain; caspase-1, cysteinyl aspartate-specific proteinase-1; AECOPD, acute exacerbation of chronic obstructive pulmonary disease; FAS, full analysis set; SAS, safety assessment set.

**Table 1 tab1:** Schedule of enrolment, intervention and assessment.

Time point	Enrollment	Allocation	Treatment phase		Follow-up
	Week-1	Week0	Week1	Week8	Week60
Assessment of eligibility:					
Eligible screen	X				
Informed consent	X				
Randomization		X			
Allocation		X			
Intervention:					
CG					
PQG					
AG					
PAG					
Primary outcome:					
6MWD		X		X	
Secondary outcomes:					
Lung function		X		X	
mMRC		X		X	
Diaphragmatic function		X		X	
MIP & MEP		X		X	
Skeletal muscle structure		X		X	
Skeletal muscle function		X		X	
HAMA&HAMD		X		X	
SGRQ		X		X	
AECOPD		X		X	X
Exploratory outcomes:					
IL-1β, IL-18, NLRP3, ASC, caspase-1		X		X	

CG, control group; PQG, pulmonary-based Qigong group; AG, acupuncture group; PAG, pulmonary-based Qigong exercise and acupuncture combined group; 6MWD, 6-min walking distance; mMRC, Modified Medical Research Council; MIP, maximal inspiratory pressure; MEP, maximal expiratory pressure; HAMD, Hamilton Anxiety Scale; HAMD, Hamilton Depression Scale; SGRQ, St. George’s Respiratory Questionnaire; AECOPD, acute exacerbation of chronic obstructive pulmonary disease; IL, interleukin; NLRP3, NOD-like receptor protein 3; ASC, apoptosis-associated speck-like protein containing a C-terminal caspase recruitment domain; caspase-1, cysteinyl aspartate-specific proteinase-1.

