### Sample size calculation

This study is a superiority trial. The sample size was calculated on the basis of 6MWD by using PASS software (version 15.0). Based on the previous clinical studies of TCEs and acupuncture intervention for COPD (19, 40, 41), the added values of 6MWD after the intervention of TCEs, acupuncture, and exercise-combined therapy were estimated to be 34.5, 32, and 38, respectively, with the assumption that the mean value of 6MWD in the control group was 297.9 and the standard deviation was 37.4. By setting alpha to 0.0083 (two-sided) and the power to 0.80, a minimum sample size of 26 participants per group was calculated. Considering a 20% attrition rate, a total of 132 participants with 33 participants per group is a reasonable sample size for this study.

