#### Secondary outcomes

Lung function will be assessed using a spirometer (MasterScreen-Body/Diff, CareFusion Germany 234 GmbH, Germany) by a professional technician in accordance with the American Thoracic Society/European Respiratory Society guidelines (49). The outcomes include forced vital capacity, forced expiratory volume in 1 s/forced vital capacity (FEV1/FVC), predicted FEV1% (FEV1%pred), forced expiratory flow at 25% of forced vital capacity predicted (FEF25%), FEF50%, FEF75%, and maximum mid-expiratory flow after bronchodilator inhalation.The degree of dyspnea in patients will be measured using the modified Medical Research Council Dyspnea Scale, which is a 5-point scale (0–4) on which higher scores indicate worse levels of dyspnea (42).Diaphragmatic function will be evaluated by a color Doppler ultrasonic diagnostic apparatus (Aplio i900TUS-AI900, Canon, Japan) with a linear array probe (10–18 MHZ, i18LX5) in M-mode. Two experienced and trained sonographers will perform the procedure. First, the sonographer will instruct the patients to assume a seated position and place the probe at the junction of the right anterior axillary line and the 7th–9th intercostal space, ensuring that the sampling line is perpendicular to the diaphragm (50). Subsequently, precise adjustments will be made for each individual to optimize visualization of dynamic diaphragmatic images. Finally, clear and stable recordings of dynamic diaphragmatic images under resting breathing will be obtained. The diaphragm thickness at end-expiration and end-inspiration (the distance between the parallel hyperechoic medial sides of the diaphragm) and the contraction velocity of the diaphragm (displacement/time) will be measured and recorded by the sonographer. The measurements will be repeated three times, and the average value will be taken. Besides, the diaphragm thickening ratio ((mean thickness at end-inspiration – mean thickness at end-expiration)/mean thickness at end-expiration) will be calculated and recorded.The maximal inspiratory pressure (MIP) and maximal expiratory pressure (MEP) of respiratory muscle strength will be measured using a respiratory muscle strength tester (TA1, BreathHome, China). The patients will be asked to use a mouthpiece to ensure no air leakage in the mouth and nose. After breathing stably, the patients will be asked to inhale hard and quickly for more than 3 s, and the MIP will be automatically calculated by the software. After breathing stably, the patients will exhale hard and quickly for more than 3 s, and the MEP will be automatically calculated by the software. The measurements will be repeated three times with a 1-min rest interval to take the best value.Skeletal muscle structure will be measured by a color Doppler ultrasonic diagnostic apparatus (Aplio i900TUS-AI900, Canon, Japan) with a linear array probe (10–18 MHZ, i18LX5) in M-mode. First, The patients will be asked to lie in a supine position, breathe calmly, with their upper limbs extended and palms up and naturally placed at the side of the body. The probe will be placed at the middle and upper 1/3–1/2 of the starting and end points of the biceps brachii muscle to collect clear and stable images. The thickness of the soft tissue in front of the humerus and the cross-sectional area of the biceps brachii muscle will be calculated and recorded. Second, the probe will be placed at 1/2–3/5 of the distance from the anterior superior iliac spine to the upper edge of the patella to collect clear and stable images of the patient in supine position while the lower limb is extended. The thickness of the soft tissue in front of the femur and the cross-sectional area of the rectus femoris muscle will be calculated and recorded. All the above tests will be repeated three times, and the average value will be taken.Skeletal muscle function will be assessed using an isokinetic muscle strength testing system (HUMAC NORM, CSMi, American) and a wireless bio-signal acquisition system (Delsys Inc., Boston, United States) to evaluate the strength and endurance of the major skeletal muscles of the upper and lower limbs. Isokinetic muscle strength tests will be performed at slow (60°/s) and fast (180°/s) angular velocities on the elbow and knee joints separately by a technician in accordance with the manual of the instrument. At an angular velocity of 60°/second, the patients will be instructed to perform five consecutive flexion and extension exercises with their maximum effort within the designated range of motion, and peak torque will be recorded. At an angular velocity of 180°/second, the patients will be asked to complete 30 consecutive flexion and extension exercises with their maximum effort throughout the entire range of motion, and total work and fatigue index are recorded. Moreover, surface electromyography signals from two 6-s maximal static contraction tests and one exhaustive static contraction test will be collected for analysis to measure the root mean square, median frequency, and mean power frequency.The psychological states of the participants will be evaluated using the Hamilton Anxiety Scale (HAMA) and the Hamilton Depression Scale (HAMD), which will be completed through self-assessment (51). The HAMA, consisting of 24 items scored from 0 to 4, will assess anxiety symptoms. The HAMD, consisting of 24 items rated on a scale of 0–2 or 0–4, will evaluate depressive symptoms. Higher scores indicate higher levels of anxiety and depression.QoL will be assessed utilizing the St. George’s Respiratory Questionnaire, a specific assessment tool for patients with COPD (52). This questionnaire comprises a total of 50 questions that cover three main aspects: symptoms, activities, and effect on daily activities. Each question is scored on a scale ranging from 0 to 100 on the basis of its significance, with lower scores indicating no impairment and higher scores indicating extreme impairment.The frequency and severity of AECOPD 1 year before and after the intervention will be recorded.

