
#### Exploratory outcomes

A 10 mL venous blood sample will be collected from the patients under fasting conditions before and after the 8-week intervention. Plasma and serum samples will be stored at −80°C as required. The levels of inflammatory cytokines interleukin (IL)-1β and IL-18 will be tested using ELISA kits. The content of NOD-like receptor protein 3 (NLRP3), apoptosis-associated speck-like protein containing a C-terminal caspase recruitment domain (ASC), and cysteinyl aspartate-specific proteinase (caspase)-1 will be measured using polymerase chain reaction.

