### Statistical analysis

An independent statistician who is not involved in outcome measurement will perform statistical analysis using SPSS software (version 24.0). All participants will be included in the intention-to-treat analyses. The multiple imputation method will be utilized to analyze missing data. Continuous data will be expressed as mean ± SD or median ± quartile interval, and enumeration data will be expressed as a relative ratio. Comparisons of baseline differences between groups will be performed using ANOVA or the Kruskal–Wallis H test for continuous variables and χ2 for categorical variables. Comparisons within each group (before and after 8 weeks of intervention) will be evaluated using a paired t-test or non-parametric test. Comparisons of endpoint differences between groups will be assessed using a 2 × 2 ANOVA (group × time) or the Kruskal–Wallis H test, with analysis of covariance applied when baseline is not uniform. In addition, a Difference-in-Difference (DID) analysis will be conducted to further assess the intervention effects while accounting for baseline differences and time trends.Multiple comparisons between the intervention arms will be performed using SNK-q test or the Nemenyi test. A *p* value of <0.05 will be considered statistically significant.

To further evaluate the discriminatory ability of each intervention in improving exercise tolerance, the area under the receiver operating characteristic curve (AUC) will be calculated for each intervention group, using the improvement in 6MWD as the classification criterion. Treatment effectiveness will be defined as an improvement in 6MWD ≥ 54 meters (minimal clinically important difference) (55). AUCs will be compared using the DeLong test with MedCalc software (MedCalc Software Ltd., Ostend, Belgium). A *p* value of <0.05 will be considered statistically significant.

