### Adverse events

All adverse events will be recorded in the case report form throughout the trial. Adverse events related to exercise and acupuncture (such as muscle and joint injuries, severe pain, local hematoma, infection, and abscess), including discomfort after treatment, will be promptly and in detail recorded. The assessor will collect from the patient a detailed description of the category and severity of the adverse event, and any correlation with the treatment. If an adverse event is serious and related to the trial, the patient will be withdrawn from the study and receive appropriate medical care.

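### A serious trial-related adverse event ends study participation, not just treatment, so obtainable outcome and safety data could be lost for a treatment-linked reason

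*Protocol article*

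**What the plan says.** The Adverse events section sets the rule: "If an adverse event is serious and related to the trial, the patient will be withdrawn from the study". The sentence goes on to promise suitable medical care. The same section says that adverse events are recorded for the whole trial, and its examples of related events are injuries and complications of exercise and needling.

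The Statistical analysis section states "All participants will be included in the intention-to-treat analyses" and "The multiple imputation method will be utilized to analyze missing data".

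On timing, the Study design section states "Outcomes will be measured within 1 week before and after the interventions". Table 1 gives 6MWD, the primary outcome, one post-baseline assessment, at week 8. Exacerbations are recorded at baseline, week 8 and week 60, and the Secondary outcomes section adds "The frequency and severity of AECOPD 1 year before and after the intervention will be recorded". No section describes assessments or safety follow-up for a patient withdrawn under the adverse-event rule.

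**The concern.** Stopping a treatment and leaving a study are different events. An intention-to-treat comparison depends on the first not causing the second. Here the protocol makes it do so for patients who have a serious event attributed to the trial.

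Three features make this more than a wording preference:

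- **Single post-baseline measurement.** A patient withdrawn before week 8 has no later walk distance to inform the imputation.
- **Trigger linked to treatment.** The active arms add 24 exercise sessions, 24 acupuncture sessions or both (three per week for 8 weeks), so the losses would fall mainly there. They would not fall there exclusively, because controls also undergo the walk test, maximal muscle tests and blood sampling.
- **Probable link to outcome.** A serious muscle or joint injury plausibly shortens walking distance. Imputing from patients without such an event would then tend to be too favourable to the arm.

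At stake are avoidable and possibly informative missing data on the primary outcome, and the loss of later exacerbation and safety data in the patients for whom safety follow-up matters most. A statistical analysis plan cannot recover data that the protocol tells staff to stop collecting.

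**Working it through.** **Reading the sections together.** The adverse-event rule ends participation. The analysis section keeps everyone in the analysis set and imputes what is missing. The two are compatible, so there is no contradiction about the analysis set. The effect of combining them is that values which could have been observed are replaced by imputed ones.

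**The plan's own figure.** The Sample size calculation section gives assumed gains: "the added values of 6MWD after the intervention of TCEs, acupuncture, and exercise-combined therapy were estimated to be 34.5, 32, and 38, respectively". The SD is 37.4, alpha 0.0083 (two-sided) and power 0.80, giving 26 per group, and 33 per group after 20% attrition. A four-group one-way ANOVA F-test with gains 0, 34.5, 32 and 38 reproduces this: n = 26 per group has power 0.810, 26/0.8 = 32.5 rounds up to 33, and 4 × 33 = 132. The concern does not affect this figure.

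**Inputs that must be assumed.** The documents give no rate of serious related events and no outcomes for such patients. I take k = 1 to 3 withdrawals among 33 patients in an arm. I take an imputed 6MWD change that exceeds the true change by s = 20, 38 or 54 m. The 38 m value represents no gain instead of the planned combined-therapy gain. The 54 m value is simply a pessimistic choice; in the protocol it is a responder threshold.

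**Overstatement of one arm's mean = (k/33) × s:**

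| s (m) | k = 1 | k = 2 | k = 3 |
|---|---|---|---|
| 20 | 0.61 | 1.21 | 1.82 |
| 38 | 1.15 | 2.30 | 3.45 |
| 54 | 1.64 | 3.27 | 4.91 |

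**Against the planned effects versus control.** The largest value is 4.91/32 = 15.3% of the acupuncture effect and 4.91/38 = 12.9% of the combined effect.

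**Against sampling error.** The standard error of a pairwise difference is 37.4 × √(2/33) = 9.21 m, so every value in the table is below it.

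**Combined versus Qigong.** The planned difference is 38 − 34.5 = 3.5 m. The net bias is ((k₁ − k₂)/33) × s. At s = 54 m:

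- 1 versus 1 withdrawal: 0 m
- 2 versus 1: 1.64 m
- 2 versus 0: 3.27 m
- 3 versus 0: 4.91 m

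The bias approaches the planned difference only when losses are uneven and the shortfall is large. Equal losses with equal shortfalls cancel.

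**Exacerbations and safety.** The documents give nothing from which to derive a size or direction of bias for exacerbations. What can be said is that recording them needs no walk or strength test, so most affected patients could still contribute. As written, the rule forgoes this.

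**The case against.** The strongest reply has five parts.

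- **The text may mean less than it says.** It does not state that assessments stop, it pairs withdrawal with medical care, and it says adverse events are recorded for the whole trial. The authors may have meant treatment discontinuation, and an article may omit post-withdrawal procedures. That intention is possible, but the article states the rule itself and not merely its details, and nothing in it limits withdrawal to treatment. How much is lost does depend on staff applying the rule literally.
- **Such events should be rare.** An event must be both serious and related, severe comorbidity is excluded, and exercise intensity may be reduced. This stands: three withdrawals in one arm and none in another is a pessimistic case.
- **Not all of the loss is avoidable.** Some patients could not do a maximal walk at week 8 even if kept in follow-up. This stands, so the metre figures are upper bounds on what the rule itself causes.
- **Combined versus single therapy cannot be resolved anyway.** The planned 3.5 m is 3.5/9.21 = 0.38 standard errors, which gives power of about 7% at two-sided 0.05 and about 1% at 0.0083. Even 3.5 + 4.9 = 8.4 m is under one standard error. This limits the practical effect on that test. The comparison is still part of the trial's stated hypothesis, and its estimate will be read.
- **The attrition allowance covers the losses.** It covers up to 33 − 26 = 7 patients per arm. That protects power but does not remove bias.

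None of this touches the loss of week-60 exacerbation and later safety data, which is the firmest part of the concern.

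**Conclusion.** The concern holds. The protocol sets an explicit rule that, followed literally, ends collection of obtainable outcome and safety data for a reason linked to treatment and probably to outcome. It weakens intention-to-treat follow-up without contradicting the analysis set.

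Under the assumed inputs, the effect on an arm's mean 6MWD change is between 0.6 and 4.9 m at most. That is unlikely to change a conclusion against control, and it matters for combined versus single therapy only if losses are uneven. The surest cost is the loss of exacerbation and safety follow-up in the patients who were harmed. Its effect on the exacerbation comparison cannot be sized or signed from the documents. The change should be made because it is cheap and protects data, not because a large bias has been shown.

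**What to change.** Reword the sentence in the Adverse events section along these lines: after a serious adverse event related to the trial, the study intervention is discontinued and appropriate care given; unless the patient withdraws consent, week-8 assessments continue where medically feasible, exacerbations are recorded to week 60, and safety follow-up continues.

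This costs one sentence. Clinical protection is unchanged, and the week-8 and week-60 contacts are already scheduled for every participant. The downside is a small effort to retain a few patients, some of whom may be unable to do the walk or strength tests at week 8. The sample size is unaffected.

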### Dissemination plans

The results of this study will be fully disclosed in an international peer-reviewed journal, and all positive and negative results will be reported.

## Discussion

This paper presents a clinical study protocol aiming to investigate the effect of the combination of PQ exercise and acupuncture therapy on multisystem function in stable patients with COPD, and the results will provide effective evidence for acupuncture as an adjuvant therapy for PR.

The acupuncture points for COPD treatment were determined on the basis of acupoint selection rules found in current literature and with guidance from experts in the field. Shi et al. (31) discovered that in clinical trials, the chosen acupoints are primarily located on the back, waist, chest, and abdomen. High-frequency acupoints include Dingchuan (EX-B1), Feishu (BL13), Zusanli (ST36), and other relevant acupoints include Pishu (BL20) andShenshu (BL23). Liu Y et al. analyzed, through data mining technology, that BL13, ST36, EX-B1, and BL23 are high-frequency acupoints (56). According to the Clinical Application Guide of TCM PR for COPD, patients with stable COPD should receive acupuncture at the main acupoints, such as BL13, EX-B1, and Lieque (LU7), whereas those with excessive phlegm should be treated at ST36, Zhongwan (RN12), Fenglong (ST40), and Danzhong (RN17). The needles should be retained for a duration of 15–30 min once every 2 or 3 days over a course of 2 months (57). On the basis of the above information; under the guidance of senior acupuncture doctors in Shuguang Hospital; and considering clinical safety, high efficiency, operability, and compliance, the acupoints LU7, EX-B1, BL13, BL20, BL23, ST36 and ST40 were finally selected in this clinical trial. The intervention time was 20 min/time, three times/week, and 8 weeks. The acupoints in this study is symptomatic of the TCM pathogenesis of COPD, characterized by lung, spleen, and kidney deficiencies; phlegm turbidity; and blood stasis (58). Stimulating BL13, BL20, and BL23 can regulate the lung qi, spleen qi, and kidney qi for treating cough and asthma symptoms while improving respiratory function. ST36 is the he-sea point of Yangming Stomach Meridian of Foot that supplements spleen to nourish the lungs (59). LU7, EX-B1, and ST40 are commonly used acupoints for relieving cough and asthma (59–62). The combination of all these acupoints embodies a holistic approach in treating lung, spleen, and kidney together to tonify lung and kidney functions while strengthening earth (spleen) to generate metal (lung), ultimately facilitating expectoration, suppressing cough, and relieving dyspnea.

The anti-inflammatory effects of acupuncture may play an important role in the treatment of COPD (31, 37). Many animal studies and clinical trials have demonstrated that NLRP3 inflammasome is activated and upregulated in COPD models and patients with COPD compared with those without COPD, and that it is involved in the occurrence and progress of chronic inflammation in COPD (63–66). The NLRP3 inflammasome, consisting of NLRP3, ASC, and caspase-1, plays a crucial role in innate immunity. Upon sensing signal stimulation, the NLRP3 protein acts as a scaffold to bind ASC. Subsequently, ASC recruits and cleaves pro-caspase-1 into its active form, leading to the processing, maturation, and release of inflammatory factors such as IL-1β and IL-18 (67). Zou and Liu et al. (68, 69) discovered that 2 weeks of acupuncture therapy at BL13 and ST36 could downregulate the protein expression levels of NLRP3, caspase-1, and ASC in lung tissues. This finding resulted in reduced levels of IL-1β in bronchoalveolar lavage fluid, alleviated lung inflammation, and improved lung injury in COPD mice. Therefore, the present study proposes that acupuncture could inhibit the activation of the NLRP3 inflammasome while reducing the protein expression levels of caspase-1 and ASC. Additionally, it could decrease the release of IL-1β and IL-18 inflammatory cytokines while mitigating lung tissue inflammation and consequently improving lung function and relieving dyspnea symptoms among patients with COPD.

In this study, 6MWD will be utilized as the primary outcome to objectively assess the functional exercise capacity of patients with COPD, which is a systemic disease with numerous extrapulmonary effects, including cardiovascular disease, frailty, and sarcopenia. Compared with FEV1%, 6MWD comprehensively reflects the intrapulmonary and extrapulmonary effects on cardiopulmonary function, skeletal muscle function, and daily physiological activity in patients with COPD (70), which in small studies has been predictive of morbidity and mortality in in patients with severe COPD (71). 6MWT is a cost-effective measure that does not require expensive equipment or complex technology. It is easy to administer, safe for subjects to perform, and well-tolerated by them. Therefore, 6MWD has been widely adopted as the primary outcome in studies related to COPD PR (72–76).

